## Abstract

Anorexia nervosa (AN) is an eating disorder that is mediated by psychological and metabolic factors, yet it is unclear how these factors interact. The NAMA trial objective is to clarify the metabo–psychiatric interaction and identify how it affects AN patients’ behaviour. This randomised trial will recruit thirty-six treatment-naïve female AN patients, 13–18 years of age, and thirty-six matched healthy controls. Participants will undergo psychiatric assessments followed by 12-h overnight fasting. The next morning, baseline assessments of outcomes will be performed. Patients will be randomly allocated 1:1 to receive a mixture with calories or receive a mixture without calories. Healthy controls will also be allocated to receive mixtures with/without calories. Mixtures will be standardised for taste and appearance, and allocation will be masked. The primary outcome measure is resting-state functional MRI 60 min post-consumption of the mixture. Secondary outcomes include (1) blood samples to study markers reflecting metabolic states, hunger/satiety and stress responses, (2) psychometric evaluations of subjective experiences and (3) assessment, in a second meal 3 h later, of the effects of previous calorie intake on subsequent food consumption. This article describes the study protocol, including the analysis plan, for a randomised controlled trial to comprehensively evaluate the effects of calorie intake in AN. The trial will distinguish psychological and metabolic neuronal networks associated with food intake and uncover how their integration affects food intake and other hallmark symptoms in AN. The aim is to accelerate treatment development by identifying brain mechanisms that drive AN.

Patients with anorexia nervosa (AN) fear gaining weight and have a distorted body image and low body weight resulting from insufficient food intake^(1)^. AN has a devastating effect on the lives of affected individuals and a markedly high mortality^(2,3)^. Onset peaks in adolescence^(4–6)^. Adolescents, at least in Western countries, often internalise a thin-body ideal^(7–9)^. Large case–control studies have associated AN with environments emphasising dieting as well as other social and personal contexts suggested to make young individuals psychologically vulnerable to AN^(9–14)^. However, many of these contextual factors are non-specific and common to other psychiatric disorders^(13)^. Additionally, most young individuals exposed to thin-body ideals do not develop AN^(15)^. Several prospective studies have failed to identify thin-body ideal internalisation and other psychological factors related to pursuing thinness as risk factors for AN^(15–18)^. Rather, it has been shown that negative affect or neuroticism and perfectionism predict AN^(12,17,19,20)^. Psychotherapy together with nutritional rehabilitation can treat AN, yet patients frequently relapse, and remission typically takes years to achieve if achieved at all^(3,21,22)^. Hence, it is unclear how psychological factors specifically affect the development and maintenance of AN^(15,23,24)^.

Emerging evidence suggests that psychological factors may interact with metabolism to precipitate AN^(25–27)^. Well-powered genetic studies have recently shown that a large part of AN heritability can be explained by a genetic architecture mediating psychiatric and metabolic traits^(28–30)^. While few AN genes have been identified so far, several of those identified are associated with metabolic signalling^(28,31–33)^. This is in line with psychometric data showing that AN patients typically feel more satiated than healthy individuals when eating food^(34–36)^. Additionally, decreasing nutrient availability by inhibiting glycolysis pharmacologically made patients with AN feel satiated, not hungry, as it did for healthy controls^(37)^. To distinguish unspecific psychological reactions from the metabolic signalling effects of nutrients, a gastric load experiment blinded AN patients and healthy controls to receive either glucose or water through a nasogastric tube. The more glucose AN patients received, the more they experienced a dose-dependent exaggerated satiety, higher fear of being fat and marked activation of the corticotropic stress pathway^(38)^. Although in AN most peripheral hormonal pathways respond as expected to a low nutritional state and reverse upon weight gain, these and other observations indicate that AN is associated with a perturbed response to metabolic signals of food intake^(25,39)^.

The perturbed response to metabolic signals in AN is associated with altered brain activity^(40–42)^. Genes linked to AN are functionally enriched for expression predominantly in brain neurones^(28,43)^. Neurones in the hypothalamus constitute a major metabolic control hub for caloric intake^(44)^. The hypothalamus has been shown to react differently to both blinded gastric loading with glucose and sucrose tasting in AN^(42,45)^. Feeding reduces the hypothalamic levels of the intracellular metabolites glutamate and glutamine in AN patients. This is paradoxical as feeding instead increases them in normal weight and constitutionally lean individuals^(46)^. Chemogenetic activation of the metabolically regulated agouti-related peptide-expressing neurones in the hypothalamus can ameliorate the development of activity-based anorexia, a mouse model of voluntary self-starvation and other hallmark AN characteristics^(47)^. AN also affects the processing of metabolic stimuli in brain areas critical for reward and emotional regulation, such as the amygdala and ventral striatum, as well as parts of the cortex mediating cognitive aspects of food intake^(41,42,45,48–50)^. Functional connectivity analyses indicate that AN perturbs how different brain areas communicate in response to metabolic fluctuations^(27,42,45,46)^. This effect on how the brain processes metabolic fluctuations by integrating information from metabolic, emotional-motivational and cognitive brain areas is supported by neurocircuit mapping in rodents showing that the decision to eat is not a function of discrete areas but rather their intercommunication^(51)^. Metabolic state affects brain processing of various stimuli in patients with acute AN as well as weight-recovered individuals, indicating that how AN affects the brain response to metabolic fluctuations is part of the core AN pathology and not just a result of weight loss^(40,41,49,50)^.

While these observations indicate that neuronal networks in the brain integrate metabolic and psychological aspects of eating differently in AN, it is unclear how this perturbed metabo–psychological integration contributes to AN development and maintenance^(52)^. No previous report has, to our knowledge, revealed in what way the connection between psychology and metabolism mediates core symptoms of AN; that is, no one has distinguished either what neuronal networks respond to the psychological *contra* metabolic aspects of eating a meal or how those networks integrate their information to affect patients’ food intake, distorted body image and fear of weight gain. The identification of the mechanisms that drive AN is also hampered by the current tendency of published studies to focus on adults rather than adolescents although adolescence is the time when most patients develop AN. The ISRCTN and Clinicaltrials.gov registers (as of October 2025) record neither any recent nor ongoing trials anywhere in the world aimed to answer these questions. No current clinical trials of AN comprehensively speak to metabo–psychological mechanisms of change.

The primary objective of the Networks Integrating Anxiety and Metabolism in Anorexia Nervosa (NAMA) trial is to distinguish between the neural response to eating caloric and non-caloric meals and how this differs between newly diagnosed adolescents with AN and matched healthy controls. Secondary objectives examine the effects of caloric and non-caloric food intake on endocrine, circulatory, psychological and behavioural responses in patients with AN and healthy controls. By integrating behavioural, psychological and physiological aspects of food intake with brain network analyses, the NAMA trial will investigate what drives AN. We hypothesise that calorie-dependent changes in network activity will differ between AN patients and healthy controls and that calorie intake will predict aggravated AN-related symptoms in patients: lower food intake, worse fear of gaining weight and increased feeling of being overweight.

The NAMA trial is designed to distinguish psychological and metabolic neural networks in the brain, uncover how these are associated with food intake and explain how their integration affects food intake and other hallmark symptoms of AN. This is, to our knowledge, the first masked clinical trial studying how the metabo–psychological interaction drives the disease in first-onset, treatment-naïve patients. The NAMA trial’s ultimate aim is to accelerate treatment development for AN based on clinically integrated pathophysiological research.

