### Intervention protocol

Depending on their randomisation result, participants will be asked to consume one of two jellies, both composed by a dietitian and prepared by study personnel: one containing 400 kcal and the other calorie-free. Both participants and the person handing out the jelly will be unaware of its caloric content. Participants will be given 15 min to consume the jelly, without forcing them to do so, and the amount consumed will be recorded.

The caloric food used in the study will be prepared using gelatine powder, water, granulated sugar, cinnamon, ginger, turmeric and grated lemon zest. To prepare the mixture, plain gelatine powder and 80 g of granulated sugar are mixed with 100 ml of hot water until a homogeneous consistency is achieved. For flavouring, one teaspoon each of cinnamon, ginger and turmeric, along with the zest of half a lemon, is added. The mixture is then brought to a boil, and after 5 min of boiling, the heat is turned off, and the mixture is left to cool for 15 min. It is then poured into a single-serving container, allowed to cool at room temperature and placed in the refrigerator for 2–3 h to solidify. The final product weighs 250 g.

The ingredients of the calorie-free food are water, agar-agar, two teaspoons of the natural sweetener Stevia, cinnamon, ginger, turmeric, grated lemon zest and lemon juice. As with the preparation of the caloric food, all ingredients are mixed and brought to a boil. After it starts boiling, it is stirred for five more minutes, and once it starts to thicken, the heat is turned off, and the mixture is left to cool for 15 min. The prepared meal is then poured into a single-serving container and refrigerated for 2–3 h until it is ready to be consumed. The final product weighs 250 g.

The ingredients and preparation methods were carefully chosen to ensure that both mixtures have a similar appearance and taste.

Three hours after consuming the first mixture (meal-1), participants will be offered a second meal (meal-2). This meal will always contain calories and consist of a nutritionally balanced, standard oatmeal dish with a distinct taste from the first meal. Participants will be allowed to eat freely, up to a maximum of 500 kcal, to minimise the risk of medical complications such as refeeding syndrome in participants with AN. Participants will have 45 min to complete the meal, and the total amount consumed will be recorded.

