##### Meal-1 and meal-2 food consumption

Although not strictly considered an outcome, the amount of mixture (in grams) consumed in the meal-1 will be recorded and included as a control variable in the analysis. The amount of food consumed in meal-2 will also be recorded by weighing the plate before and after the meal.

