The independent variables of the regression analyses will include (1) type of meal (caloric or non-caloric), (2) AN status (AN or healthy control), (3) AN subtype (restrictive or bulimic type), (4) BMI and (5) duration of AN illness. A random effect for each participant and for each matched set of patient and healthy control will be used to account for within-subject correlations from repeated measurements and dependencies within each matched pair.

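### The hypothesis counts lower meal-2 intake after calories among patients as worse AN, although ordinary satiety predicts the same; it needs a patient-control contrast

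*Protocol article*

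**What the plan says.** The paragraph on objectives and hypotheses at the end of the introduction holds two predictions. The network prediction is comparative: "calorie-dependent changes in network activity will differ between AN patients and healthy controls". The symptom prediction is stated for patients only: "calorie intake will predict aggravated AN-related symptoms in patients: lower food intake, worse fear of gaining weight and increased feeling of being overweight".

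The intake outcome is described in the Abstract as "assessment, in a second meal 3 h later, of the effects of previous calorie intake on subsequent food consumption", and under Meal-1 and meal-2 food consumption: "The amount of food consumed in meal-2 will also be recorded by weighing the plate before and after the meal". Under Intervention protocol the two jellies are "one containing 400 kcal and the other calorie-free". Meal-2 follows three hours later: "Participants will be allowed to eat freely, up to a maximum of 500 kcal".

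Under Primary analysis the independent variables include "1) type of meal (caloric or non-caloric), (2) AN status (AN or healthy control"), then AN subtype, BMI and illness duration. Secondary analyses uses similar models, and the only interaction it names is allocation by time. Table 2 schedules meal-2 intake once, at T3, so that interaction has nothing to act on there. The amount of meal-1 eaten enters only as a control variable.

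Under Randomisation, each healthy control takes the allocation of the matched patient.

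**The concern.** Before meal-1 there is a "Participants will undergo psychiatric assessments followed by 12-h overnight fasting" step, so the calorie-free arm reaches meal-2 after about 12 + 3 = 15 hours without energy. The caloric arm has had up to 400 kcal three hours earlier. Ordinary satiety predicts a lower meal-2 in the caloric arm for ill and healthy eaters alike, and the hypothesis labels that direction in advance as a worse AN symptom.

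The article's own background points to a different reading. It describes the abnormality as satiety greater than in healthy people, and as an exaggerated response to glucose. On that account the pathology is the excess over controls, not the reduction itself.

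Food intake is the first symptom in the hypothesis and the trial's behavioural outcome. If the hypothesis is tested as worded, a physiological reduction would count as support for the claim that calories worsen AN.

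**Working it through.** **Inputs from the article.** 36 patients randomised 1:1, so about 18 per arm; 36 controls with matched allocation, so about 18 per cell; two-sided 5% tests; 400 v 0 kcal in meal-1; 500 kcal cap on meal-2; adherence means more than 30% of meal-1 eaten. **Assumed, because the article gives no figures:** the size of the ordinary satiety effect, the SD of meal-2 intake and mean intake in each group. The calculations ignore covariates and matching.

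**1. The plan's own figure.** Sample size calculation gives 34 per group for d = 0.6 and 70% power. Normal approximation: n = 2(1.960 + 0.524)²/0.6² = 34.3, rounded up to 35; the exact t calculation gives 36. Power at 34 is 0.70 (normal) or 0.68 (t). The figure reproduces closely, but it concerns AN v healthy, not the effect of calories on meal-2.

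**2. Probability of a significant result when the satiety effect is the same in patients and controls.** Noncentral t, with noncentrality d√(n/2): 3d for 18 v 18 and 4.24d for 36 v 36.

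| Ordinary satiety effect (SD) | Patients only, 18 v 18 | Pooled meal effect, 36 v 36 |
|---|---|---|
| 0.4 | 0.22 | 0.39 |
| 0.6 | 0.42 | 0.71 |
| 0.8 | 0.65 | 0.92 |

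None of these results needs an AN-specific effect.

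**3. The same in kcal (simulated, meal-1 fully eaten, no cap).** If 20% of 400 kcal is compensated, meal-2 falls by 80 kcal and the patient-only test is positive with probability 0.64, 0.35 or 0.22 for an SD of 100, 150 or 200 kcal. At 40% (160 kcal) it is above 0.99, 0.87 or 0.64.

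**4. Partial consumption.** At just over 30% of meal-1, energy eaten is about 0.30 × 400 = 120 kcal, and 20% compensation is 24 kcal. With SD 100 that is 0.24 SD. The probability then lies between 0.09 (at 0.2 SD) and 0.14 (at 0.3 SD).

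**5. The patient-control contrast.** In the 2 × 2 layout with 18 per cell, the SE of the interaction is √(4/18) = 0.471 SD.
- With identical satiety in both groups and no cap, it rejects in about 5% of simulated trials, about 2.5% in the direction of a larger reduction in AN.
- Power for 0.6 SD: Φ(0.6/0.471 − 1.960) = Φ(−0.69) ≈ 0.25.
- For 70% power: 4(1.960 + 0.524)²/0.36 = 68.6, so 69 per cell.

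**6. Effect of the cap on that contrast.** Simulation with 20,000 runs, identical satiety in both groups, patients eating 250 kcal on average after the calorie-free meal, and meal-2 limited to 0–500 kcal.
- If controls would eat 450 kcal, the interaction rejects in about 5–7% of runs.
- If controls would eat 700 kcal uncapped, it falsely shows a larger reduction in AN in 13–59% of runs at 20% compensation and 26–96% at 40% (SD 200 down to 100 kcal).

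**The case against.** The design already holds the answer. Matched controls receive the same meals, the secondary objectives cover behavioural responses in both groups, AN status is in the model, and the Discussion says controls are there to make conclusions disease-specific. A reader might infer that the trial cannot separate satiety from pathology; the documents do not support that, because the data for the right contrast will exist. Nor does the article say that an 18 v 18 patient-only t test is the planned analysis; it plans regression models, and the calculation only shows what a comparison matching the stated hypothesis would do.

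The article is condensed, so a missing interaction term alone would be no finding. What stands is the stated hypothesis: an analysis plan that tested it faithfully would inherit the problem.

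A reader might also infer that only lower total energy (meal-1 plus meal-2) could count as aggravation. That goes too far. Total energy includes up to 400 kcal assigned by randomisation, and it replaces the stated question about subsequent intake. An individual compensation ratio is not available either: the trial is parallel-group, each participant has one meal-2 and no reference meal of her own, and meal-1 energy is zero in the calorie-free arm.

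Finally, the size rests on assumptions. The Discussion expects some patients to leave part of meal-1, and satiety in AN may itself be altered. Both limit the magnitudes, but neither makes a patient-only reduction specific to AN.

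**Conclusion.** The concern holds for the food-intake component. Lower meal-2 intake in the caloric arm among patients, or a pooled meal effect, can arise from ordinary satiety alone. The patient-only comparison is positive with probability about 0.22, 0.42 or 0.65 for an assumed effect of 0.4, 0.6 or 0.8 SD, against a nominal 5%, and less often where meal-1 is only partly eaten. The direction of the argument needs only a non-zero satiety effect; its size depends on the assumed effect and SD.

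The defect lies in the wording of the hypothesis and the named model terms, not in the control group or the data collected. It is tempting to extend it to fear of gaining weight and feeling overweight, which share the same sentence. Ordinary satiety does not explain those in the same way, so the point stops at intake.

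**What to change.** - Reword the intake part of the hypothesis: the calorie-dependent reduction in meal-2 intake is larger in AN patients than in matched controls. This matches the comparative form of the network hypothesis.
- Add the meal-type by AN-status interaction to the meal-2 model and report it with its 95% confidence interval.
- State that a between-arm reduction among patients alone is compatible with normal satiety.
- Report total energy from both meals descriptively if wanted, and do not define an individual compensation ratio.
- Report the number of participants at the 500 kcal cap by AN status and arm, and interpret the interaction in that light.

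No new data are needed, and no change to the meals or the cap is proposed. The cost is a harder claim: about 25% power for a 0.6 SD interaction at 18 per cell, with bias possible if controls reach the ceiling. Both should be stated as limitations, and a non-significant interaction should not be read as equal responses.

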## Experimental methods

### Design

The study is designed as a single-centre, parallel-group randomised controlled trial with two study arms: (1) calorie intake in meal-1 and (2) no calorie intake in meal-1. Participants and healthy controls are individually randomised to either one of the two arms, both delivered at the eating disorder clinic of the Ege University Hospital, Faculty of Medicine.

The primary outcome measure is brain patterns observed with functional MRI, and secondary outcomes include endocrine markers in blood, cardiovascular responses, self-reported symptom severity and subsequent food consumption.

The study is planned following the Standard Protocol Items: Recommendations for Interventional Trials^(53,54)^ and will be analysed and reported following the recommendations in Consolidated Standards of Reporting Trials^(55)^, with special care taken to meet extended recommendations for both trials with patient-reported outcomes^(56)^ and non-pharmacological trials^(57)^.

### Protocol design and conduct

This is the study protocol version 1.0, 2025-05-10. For details on the trial registration, see Table 1. To ensure transparency and integrity throughout the study, all changes or deviations from the protocol will be thoroughly documented and reported. Any modifications to the protocol, including changes to study objectives, design, participant population, sample size, procedures or significant administrative aspects, will necessitate a formal protocol amendment. Similarly, any alterations that could potentially impact participant safety, benefits or risks will be carefully evaluated and documented. Proposed amendments will be reviewed and approved by the study team and submitted for approval to the national ethical review board before implementation. Additionally, all relevant study personnel will be promptly informed of these changes to ensure compliance and consistency across the study.

**Table 1. tbl1:** Trial registration data Table 1 long description.

Data category	Information
Primary registry and trial identifying number	ClinicalTrials.gov NCT06814002
Date of registration in the primary registry	2025-02-06
Primary sponsor	Umeå University, Ege University
Contact for public and scientific queries	[name]
Public title	NAMA trial
Scientific title	Networks integrating anxiety and metabolism in anorexia nervosa trial
Countries of recruitment	Turkey
Health condition studied	Anorexia nervosa
Interventions	Meal with 400 kcal and meal without calories
Key inclusion and exclusion criteria	Inclusion criteria: female sex, 13–18 years of age, patient at the eating disorder clinic, AN DSM-5 diagnosis, treatment naïve. Healthy controls are accepted (eating disorder in the present or past is an exclusion criterion for them).
	Exclusion criteria: chronic medical conditions, medications that affect hormone levels or eating behaviours, severe psychiatric disorders other than AN, drug abuse, pregnancy, high risk of refeeding syndrome, allergies to provided meal content, cognitive impairment, contraindications for MRI, fasting blood glucose above 6·0 mmol/l on the morning of the study
Study type	Interventional
	Allocation: randomised
	Primary purpose: mechanistic research
Date of first enrolment	2025-02-15
Target sample size	72
Recruitment status	Recruiting
Primary outcome	MRI
Key secondary outcomes	Food consumption, psychometric scales, blood samples, blood pressure, pulse

AN, anorexia nervosa, DSM-5, Diagnostic and Statistical Manual of Mental Disorders, 5th edition, kcal, kilocalorie.

